### Consent

All participants will be recruited by a qualified and delegated member of the research team trained in Good Clinical Practice (GCP). Consent to enter the study will be sought from each participant only after a full explanation has been given, an information pack offered, and time allowed for consideration. Signed consent will be obtained from participants before any study specific assessment or investigation.

Participants, or their carer/parent will be approached about this study early during their stay by a member of the research team and receive the study information pack. This will either be in person or remotely via video conferencing. Hence, they will have sufficient time to have all their questions addressed by the study team to decide whether to participate. They will have the opportunity to discuss the study and ask questions at any stage of the procedure. The information leaflets have been reviewed by several parents/carers of children with mitochondrial disease. The overall feedback has been positive, and the material was described as noticeably clear with enough information needed to make an informed choice. A copy of the signed informed consent form will be provided to the participant and a copy filed in the participant’s hospital records. The original signed consent form will be stored in the Investigator Site File.

Consent to ongoing participation in the study will be verbally re-confirmed with the participant and documented in their medical record at each subsequent assessment point (e.g., new focal epileptic event). Participants have the right to refuse to participate without giving reasons and without prejudicing further treatment. Documents will be translated to other languages if required. An interpretation service is available in the NHS Trust should this be requested. However, if the parent/guardian is unable to fully understand the study and cannot provide informed consent they would not be eligible to take part.

Participants aged 16 years or over with the capacity to provide consent, will be consented as adults and asked to complete their own informed consent form. For participants aged under 16 years, consent will be obtained on behalf of the participant from their parent or a person with parental responsibility. Where appropriate, written assent will be obtained from the child. If a participant has their 16th birthday whilst participating in the study, they will be re-consented as an adult. If they lack capacity to provide consent, a consultee will be asked to provide a consultee declaration on the participant’s behalf. Additional consent includes permission to obtain information from medical records (until six months after study end), to obtain accelerometer data, and to obtain optional short video recordings. No biological specimens will be collected.

### Participant timeline

After consenting (legal guardian/carer) and assenting (for children who are capable), all participants will be allocated a unique study number. Several screening procedures will be performed including – basic demographics, complete medical history with physical examination and vital signs, and pre-treatment baseline assessment of seizure frequency (see Table 1). Participants who complete screening and meet all study requirements, will be randomised, and enter the treatment period on Day 1 (see Fig. 1).

**Table 1 Tab1:** Schedule of events

Procedure	Screening	Intervention	Follow-up	Frequency	Duration (mins)	Performed by:
Informed Consent	**X**			1x	45	Study team
Demographics	**X**			1x	5	Study team
Medical History	**X**			1x	15	Study team
Physical Assessment	**X**			1x	5	Study team
Confirmation of Eligibility	**X**			1x	15	Study team
tDCS		**X**		1x daily for max. 14 days	30	Study team (or trained carer)
Seizure diary	**X**	**X**		3x daily for max. 15 days	varies	Patient/carer/legal guardian
Video monitoring of seizure area (if consented)	**X**	**X**		1x daily for max. 15 days	5	Patient/carer/legal guardian
Accelerometery recordings	**X**	**X**		2x	Continuous	Patient/legal guardian/ or study team
Adverse Event Reporting	**X**	**X**	**X**	Max. 15 days	20	Study team
End-of-study EEG			**X**	1x	30	Study team

*Note* Administration of tDCS will end with resolution of the focal epileptic event (i.e. seizure freedom), or after 14 days, whichever happens earlier

**Fig. 1 Fig1:**
[figure not shown]
Overview of study events. Please note that patients will only receive the MRI procedure if considered necessary from a clinical point of view as part of the patients’ regular care

## Intervention procedures

### Randomization and intervention protocol

At baseline, participants will be randomly assigned to receive either sham stimulation (delayed-start group) or active tDCS (early-start group). The placebo group will receive double-blinded sham procedure for 2 days. On Day 3, all participants will receive the active tDCS intervention as an adjunctive treatment for up to day 14. The allocated intervention will not be modified.

At baseline, participants will be randomly assigned to one of two arms for each focal event:

In the **Early Start Group** participants will receive 20 min of active tDCS daily from the start of the intervention period (day 1) for up to 14 days. By default, each active stimulation treatment session starts with an automated ramp up of current to 2 mA over 15 s to keep participants blind to the intervention. For the early start group tDCS then continues for 20 min until it ramps down.

In the **Delayed Start Group** participants will receive sham-stimulation/placebo treatment on day 1 and day 2 of the intervention followed by up to 12 additional days of active tDCS (1x daily for 20 min). Like active tDCS, sham tDCS starts with an automated ramp up of current (from 0 to 2 mA over 15 s) to mimic the sensations observed with active tDCS and to keep participants blind to the intervention. For the sham tDCS the current stops after the 15s ramp up. This sham stimulation protocol is well supported by current literature [16, 17].

### Intervention administration and assessment procedures

Participants will undergo the following interventions and assessments as part of the study:

**Cathodal transcranial direct current stimulation (tDCS) at 2 mA**: The treatment will be administered 1x daily (every 24 h) for a period of up to 14 days. Participants will either receive active tDCS from day 1 (early-start group) or cross over from sham treatment to active tDCS on day 3 (delayed-start sham group). Neither the participant nor the treating physicians will be aware of the participants’ randomisation allocation. The scalp location for applying tDCS will be defined by the location of the epileptogenic focus responsible for the clinical seizures. Administration of tDCS will end with resolution of the focal epileptic event (i.e., seizure freedom), or after 14 days (whichever is earlier).Participants, their carers, or hospital staff will complete a seizure diary three times daily throughout the intervention period. Throughout the entire study, from Day 1 up to Day 14, seizure frequency (including onset time and duration of seizures) will be documented three times daily. This diary may also record seizure count, seizure type, frequency of twitches, potential medication changes and/or possible seizure triggers.Participants will undergo a study-specific **end-of treatment standard clinical EEG** for each focal event.**Short videos**, lasting 1–2 min, will be recorded daily throughout the treatment period to document seizure frequency in the affected body areas. Parents/carers will capture these videos following detailed instructions provided to them. Due to limited resources, it will not be possible to provide equipment on which to record videos at home therefore the ability to record videos at home will depend upon the equipment available. Participants, or their parents/carers, may opt out of video recording entirely or choose to have recordings done exclusively in the clinic.**Accelerometery (continuous throughout treatment period)**: To monitor seizure activity we will measure 3D motion data from the areas of the body that are affected by the participants’ motor seizures one day prior to the start and during the 14-day treatment period. The participant will wear accelerometers that, depending on the body parts that are affected by seizures, can either be fastened around the wrist or securely taped to the body. We will collect 3D movement, vibrations, and orientation changes to verify seizure activity. The device is waterproof and should be worn continuously during the treatment period. The device is CE safety mark approved and compliant with the Directive 2014/30/EU. Consent to wearing the device is optional.

Pre-study EEGs and brain MRIs will be acquired as part of the participants’ standard care for diagnosis and localisation of the epileptic focus. MRI and EEG safety screening questionnaires will have been completed before each exam as part of participants’ standard care. In the absence of an MRI lesion, the tDCS target will be determined based on standard clinical scalp EEG. These procedures will not be part of the study, but neuroimaging results will be considered for treatment-related decisions (e.g., specification of the tDCS target) and treatment evaluation. Only the ‘end of study’ standard clinical EEG will be collected as part of the study. Participants will receive a post-intervention MRI procedure if considered necessary from a clinical perspective as part of the patients’ routine care. Those MRI scans are not a standard research assessment related to this study but will be included in the data analysis when consent has been explicitly obtained for that purpose.

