### Intervention period

Participants who are confirmed to be suitable for continued participation in the study will then undergo the following assessments/activities:

Randomisation.tDCS for a period of 20 min once a day, for a period of up to 14 days.Completion of a seizure diary/collection of seizure events daily over the tDCS treatment period.1–2 min of daily video recordings of areas of the body affected by seizures (if consented).Continuous accelerometery measurements (in consented).

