#### Target difference and sample size

Assuming a minimum of one assessment per patient event per day, each event will contribute 14 data points over 14 days of treatment (tDCS or sham). Further assuming no association between days of treatment and reduction in epilepsy events, the outcome data are treated as clustered data for the purposes of the power calculation. Assuming 5% type I error, 90% power, and 10% intra-patient correlation, 28 patient events will be required over 14 days of treatment to detect an improvement of 20% in events that achieved 50% reduction in seizure frequency. The sample size calculation also assumes that only 10% of the events in the placebo group will achieve 50% reduction in epilepsy frequency from baseline (on day 0). To account for drop-out, 30 patient events will be required for this study. The patient events will be allocated equally to active and sham tDCS groups. These calculations were determined based on clinical significance, patient perspectives, historical data, statistical considerations, and regulatory guidelines [25].

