## Discussion

### Study design, practical and operational challenges

Refractory focal epilepsy associated with a mitochondrial disorder, while rare, often has a poor prognosis. Here, we address the unique challenges encountered in designing a randomized, sham-controlled study within the context of rare diseases.

First, designing this randomised sham-controlled study has posed ethical challenges of administering a treatment to one group and not another while keeping high methodological stringency. Our team’s prior treatment of five patients with mitochondrial epilepsy, who had received cathodal tDCS on compassionate grounds, suggests that focal episodes may resolve within the first three days of stimulation [27]. Based on that, we adopted a delayed-start design. One group receives the treatment immediately (early-start), while the delayed-start group receives a non-active (sham) treatment for the first two days and then receives active treatment from day 3.

Secondly, recruiting patients with a condition classified as a rare disease who experience an acute event is logistically challenging and, in this case, requires active recruitment methods. Potential participants will be identified by their health care provider while patients are admitted to the hospital for an acute focal epileptic event that remains unresolved by antiepileptic drugs. Consequently, the timeframe of recruitment is unpredictable, and to complete recruitment within the 3-year study period, individual means of recruitment may be considered.

Third, for some participants admission to our premises could be disruptive e.g., if their symptoms can be managed externally. To not exclude any potential participants from entering the study, we consider remote treatment for those patients. In that case patients would be referred to our site for their tDCS treatment. After initial supervised device training, tDCS will be self-applied by patients at home or in their care setting, under the remote supervision of a medical professional. Depending on the participants’ circumstances, we will determine individually which option is least disruptive.

Fourth, patients exhibit various types of seizures, each requiring unique methods of recording and diagnosis. To ensure optimal daily monitoring of seizure activity, we maintain close monitoring of the patient, provide flexible seizure diary templates, and record relative values.

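### The protocol contradicts itself on whether seizure recording continues after an episode resolves; if it stops, the 14 data points per event behind the stated power are not collected

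*Protocol article*

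**What the plan says.** **Treatment.** In Intervention administration and assessment procedures: "Administration of tDCS will end with resolution of the focal epileptic event (i.e., seizure freedom), or after 14 days", whichever is earlier. The note to Table 1 (Participant timeline) repeats this for tDCS.

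**Recording tied to treatment.** Intervention period lists "Completion of a seizure diary/collection of seizure events daily over the tDCS treatment period". In Intervention administration and assessment procedures, participants, carers or staff "will complete a seizure diary three times daily throughout the intervention period". Post-intervention places the closing EEG on the day after the last intervention day.

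**Recording on a fixed calendar.** The next sentence of Intervention administration and assessment procedures begins "Throughout the entire study, from Day 1 up to Day 14, seizure frequency" and has it documented three times a day. The same section describes accelerometry over a 14-day treatment period.

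**A ceiling only.** Table 1 gives the diary as "3x daily for max. 15 days", with no rule for an episode that resolves early.

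**Sample size.** Target difference and sample size assumes that "each event will contribute 14 data points over 14 days of treatment (tDCS or sham"). It continues: "Assuming 5% type I error, 90% power, and 10% intra-patient correlation, 28 patient events will be required over 14 days of treatment".

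**Expected speed of response.** The Discussion says that the team's experience with five patients "suggests that focal episodes may resolve within the first three days of stimulation". This is the stated reason for the delayed-start design.

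**The concern.** If the diary follows treatment, recording ends at the moment of success. An event that resolves on day 3 gives about three daily outcomes and an unresolved one gives 14. Three things follow.

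- The primary analysis is a GEE on the binary 50% reduction. Its cluster size would then depend on the outcome, and the two arms would differ in the number of days observed.
- A relapse after stimulation stops would not appear in the daily data, although the endpoint is a daily frequency compared with day 0.
- The sample size counts 14 data points from every event, so the planned information would not be reached.

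Early resolution is the outcome that the design anticipates, so this would not be confined to a few unusual events. It is also a matter of data collection: days never recorded cannot be recovered by any later analysis plan.

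**Working it through.** **1. Reproducing the 28 events.** Inputs from Target difference and sample size: response 10% against 30% (10% plus 20 points), 5% type I error (taken as two-sided), 90% power, correlation 0.10, 14 data points per event, equal allocation.

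Independent observations per arm, pooled-variance formula without continuity correction:

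n = [1.960·√(2·0.2·0.8) + 1.282·√(0.1·0.9 + 0.3·0.7)]² / 0.2² = 81.96, so 82.

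Design effect = 1 + (14 − 1)·0.10 = 2.3. Events per arm = 82·2.3/14 = 13.5, so 14 per arm and 28 in total. This matches the protocol.

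**2. Same formula with fewer data points.** With m data points per event and k events per arm, the effective sample per arm is n_eff = k·m / [1 + (m − 1)·0.10], and

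power = Φ{[0.2·√n_eff − 1.960·√0.32] / √0.30}.

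The values of m below 14 are assumptions; the protocol gives no distribution of time to resolution.

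| m | Design effect | n_eff per arm (28 events) | Power, 28 events | Power, 30 events | Events needed for 90% |
|---|---|---|---|---|---|
| 14 | 2.3 | 85.2 | 91% | 93% | 28 |
| 8 | 1.7 | 65.9 | 83% | 85% | 36 |
| 5 | 1.4 | 50.0 | 71% | 74% | 46 |
| 3 | 1.2 | 35.0 | 55% | 58% | 66 |

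Example, m = 5: 14·5/1.4 = 50; (0.2·7.071 − 1.109)/0.548 = 0.56; Φ(0.56) = 0.71. The formula takes m as the same for all events and unrelated to outcome, so it shows only the loss of information.

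**3. Direction of bias.** A simulation in the delayed-start layout (sham on days 1–2 in one arm, active in both from day 3) moved each event daily between non-responder, responder and resolved, with between-event variation and a 10% daily chance of losing response. Full 14-day recording was compared with recording cut at resolution, using 20,000 events per arm for risk differences and 1,500 per arm for GEE fits. All rates are assumptions. Moderate means a 25% daily chance of each forward step on active; fast means 60% (50% in the relapse row); sham is 5% throughout.

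| Scenario | Risk difference, full → cut | Log OR, full → cut (independence) | Log OR, full → cut (exchangeable) |
|---|---|---|---|
| Moderate, no relapse | 0.089 → 0.071 | 0.46 → 0.33 | 0.46 → 0.48 |
| Fast, no relapse | 0.123 → 0.178 | 0.89 → 0.76 | 0.89 → 1.10 |
| Fast, relapse 10% per day after stopping | 0.048 → 0.146 | 0.20 → 0.55 | 0.20 → 0.89 |
| Moderate, relapse 30% per day after stopping | 0.020 → 0.072 | 0.16 → 0.34 | 0.16 → 0.49 |

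Mean days recorded per event fell from 14 to between 4.5 and 9.2. Without relapse, the independence log odds ratio shrinks and the exchangeable one grows slightly or more. With relapse, every measure moves away from the null.

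**4. Days 1–2, the only sham-controlled days.** In this simulation their contrast was unchanged, but only because no event could resolve before day 2. Now allow resolution on day 1: daily resolution 20% on active and 2% on sham, with 20% and 10% responder-days before resolution (assumptions).

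- Full recording, active: day 1 is 0.20 + 0.80·0.20 = 0.360; day 2 is 0.36 + 0.64·0.20 = 0.488; mean 0.424.
- Full recording, sham: day 1 is 0.02 + 0.98·0.10 = 0.118; day 2 is 0.0396 + 0.9604·0.10 = 0.136; mean 0.127. Difference 0.30.
- Cut at resolution, each recorded day has the day-1 rate: 0.360 − 0.118 = 0.24.

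So the early contrast is protected only if nothing resolves on day 1.

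**The case against.** The strongest reply is that the stopping rule governs stimulation and not the diary. The sentence on documenting seizure frequency from day 1 up to day 14 can be read as a fixed window, the accelerometry text uses a nominal 14-day period, the note in Table 1 applies to tDCS alone, and 14 data points per event fits only a fixed window. On that reading the diary already runs to day 14. This stands as a possible reading, so it cannot be said that recording definitely ends at resolution. It does not settle the matter: the entry under Intervention period contradicts it, the protocol uses the same up-to wording for maximum treatment length, and the 15 days in Table 1 are only a ceiling.

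A reader might infer that cutting observation at success must bias the effect towards the null. The simulations do not support that: the sign changes with the working correlation, the speed of response and relapse, and the article does not fix a working correlation. A reader might also infer that relapse goes unseen. That is too strong, since six months of medical-record data are collected and some participants are inpatients. Those records would catch some relapses, but they are not a daily frequency.

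It can also be said that scoring days after resolution belongs in the analysis plan. That is fair for the scoring, but not for whether the data are collected.

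**Conclusion.** The point holds as an unreconciled contradiction with a material consequence on one of its two readings. If recording continues to day 14 for all events, the sample size stands and only the wording needs repair. If it stops at resolution, observations per event depend on the outcome, daily relapse data are lost, and the 14-day estimate is biased in an uncertain direction. The stated 90% power with 28 events would not hold: about 83%, 71% or 55% with 8, 5 or 3 data points per event. These powers rest on the protocol's own inputs, a two-sided test and assumed values of m, and they ignore the link between cluster size and outcome. The simulated biases rest wholly on assumed rates; they show that the direction is not fixed, and they do not predict its size in this trial. A claim that the diary certainly stops, or that the effect is certainly diluted, would go beyond the documents.

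**What to change.** Reconcile Table 1, Intervention administration and assessment procedures, Intervention period, and Target difference and sample size by stating two things:

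1. The seizure diary, and the accelerometer where consented, continues to day 14 for every event, whether or not stimulation has stopped.
2. Days after resolution enter the primary analysis with their recorded responder status, relapse included.

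If recording is instead meant to stop at resolution, say so and restate the power with a realistic number of data points per event.

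The treatment stopping rule need not change. The cost is some extra diary days for events that resolve early, within the 15 days already allowed, and a sentence or two in the protocol and the analysis plan.

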### Intervention procedure

Participants will be seated and their skin on the scalp around the stimulation areas will be inspected to ensure it is healthy and intact. Any metallic objects (hairpins, glasses, jewellery) near the electrodes will be removed. The tDCS system will be visually inspected, including checking the battery status. According to the participant’s head circumference a suitably sized neoprene cap with chinstraps will be selected. Based on the participants’ seizure location, electrodes will be attached to the cap. A medical professional will determine electrode location individually for each focal event, based on the MRI, EEG, and patient history. Electrode location is determined prior to the treatment and remains the same throughout the study for each focal event. Electrodes will be clipped onto the pre-determined position. As a rule, the cathode will be located over the seizure site and the anode maximally distant to the seizure site. To avoid mix-ups of electrodes, we customize caps with marked insertion holes for the electrodes at each stimulation location, we provide in-person training, customised written instructions and remote video guidance. The cap will be placed on the participants head with a conductive medium (15 ml of NaCL 0.9%) applied between electrode and scalp. The device will be placed safely (away from liquids, no tripping hazards etc.). Spillage of the conductive medium will be avoided by removing any excess electrolyte before application to the head. We will control the position of electrodes and caps before treatment starts to keep the optimal treatment constant over the entire study. Stimulation will only start if the impedance is below 15 kΩ. Stimulation will automatically be paused if impedance increases above this threshold. The device times the treatment and automatically stops current flow after 20 min. Throughout the therapy session, impedance and current flow will be monitored.

